**2.2 Number of Centres**

This is a multiple centre study which will take place at the Maprik Hospital, East Sepik Province, and at Yagaum Health Center, Madang Province, Papua New Guinea.

**3 SUBJECT SELECTION FOR STUDY ENTRY**

**3.1 Population Base**

Subjects will be selected from people continuously exposed to malaria, living in the catchment area of the Maprik Hospital and Yagaum Health Center.

**3.2 Inclusion Criteria**

Willingness of the adults, parents or legal guardian for children, to give informed consent is the primary criteria for inclusion.

Other inclusion criteria will be : persons presenting at the outpatient clinic or admitted in the ward, aged > 6 months, with fever or history of fever in the last three days, and no other major symptom or sign, with a clinical diagnosis of malaria, an OptiMAL test positive (for whatever species), and with a documented (in the health book) episode of malaria treated with standard drugs in the last 28 days.

**3.3 Exclusion Criteria**

A subject is not eligible if one or more of the following parameters are fulfilled:

- History of allergy to drug compounds
- Unable to swallow
- Signs of severe malaria (i.e. history of recent convulsion, any neurological sign or impairment of consciousness, temperature >40 C0, heavy vomiting, , haemoglobinuria, respiratory distress, bleeding, circulatory collapse, shock, jaundice, haemoglobin < 5 g/dl)
- Contra-indications for Lariam (history of psychiatric disorder, epilepsy)
- Less than 6 months of age
- Pregnancy

**3.4 Subject Screening**

During the screening phase, subjects are to be identified by their name.

A screening log must be kept by the investigator, in which the eligibility status of **every** subject screened must be recorded, regardless of whether or not they enter the study. To maintain confidentiality, subjects need only be identified by their initials.

**4 DESCRIPTION OF TRIAL DRUG**

The drug is produced by Fatol Arzneimittel GmbH.

**4.1 Names and Formulations**

Cotrifazid is a combination made of rifampicin 112.5 mg, sulphamethoxazole 200 mg + trimethoprim 40 mg, and isoniazid 75 mg.

**Galenical Form and Strength.**

Cotrifazid is a coated tablet.

**4.2** **Packaging, Storage and Blinding**

The drug is stored at room temperature.

Investigators and subjects are aware of the treatment allocation, i.e. Cotrifazid, Lariam or standard treatment.

**5** **STUDY PROCEDURES**

**5.1 Drug**

**5.1.1 Drug Administration**

**5.1.1.1 Dosage Regimen & Rationale for Selection**

The treatment dosage and schedule for Cotrifazid will be the following : subjects > 40 kg 2 x 2 tablets, subjects < 40 kg and > 20kg  2 x 1 tablet, subjects < 20 kg  2 x ½ tablet, every 12 hours.

The treatment dosage and schedule for Lariam will be the following : subjects > 60 kg : 6 tabs (3 at hour 0, 2 at hour 8, 1 at hour 24), subjects > 40 kg and < 60 kg : 5 tabs (2, 2, 1), subjects < 40 kg and > 30 kg : 3 ½ tabs (1 ½ , 1, 1), subjects < 30 and > 20 kg : 3 tabs (1, 1, 1), subjects < 20 kg and > 10 kg : 1 ½ tabs ( ½ , ½, ½ ), subjects < 10 kg : ¾ tablet ( ¼ , ¼, ¼ ).

The treatment dosage and schedule for quinine will be the following : subjects > 60 kg  3 x 600 mg quinine /day, subjects < 60 kg  3 x 10 mg/kg/day every 8 hours.

The treatment dosage and schedule for Fansidar will be the following : subjects > 40 kg  3 tablets, subjects < 40 kg and > 30 kg 2 tablets, subjects < 30 and > 20 kg 1 ½ tablet, subjects < 20 kg and > 10 kg 1 tablet, subjects < 10 kg ½ tablet.

**5.1.1.2 Route of Administration**

Cotrifazid, Lariam and Fansidar will be given orally.

Quinine will be given orally or intramuscularly..

**5.1.1.3 Duration**

Cotrifazid will be given for 7 days.

Lariam will be given for 24 hours.

Quinine will be given for 5 days.

Fansidar will be given as a single dose at day 0.

**5.1.1.4 Dispensing of Trial Drug**

The administration of the drug for the first three days will be supervised by the nurse in charge of the trial.

All drug supplies are to be returned to Fatol Arzneimittel GmbH.

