**INVESTIGATORS**

Principal Investigator: [name] MD PhD MSc DTM&H

Clinical epidemiologist, Department of Medical Parasitology and Infection Biology

Swiss Tropical Institute

[name]

Postfach

[name]

Telephone number: [name]

Fax number: [name]

Email : [contact]

Co-principal investigator : [name] MD

Papua New Guinea Institute of Medical Research

[name]

Maprik Papua New Guinea

Telephone number: [name]

Fax number: [name]

Email : [contact]

PROTOCOL TITLE Efficacy and tolerance of COTRIFAZID (rifampicin, co- trimoxazole, isoniazid) against resistant malaria in semi-immune subjects: a multicentric, open, block- randomised, comparative trial

PROJECT PHASE III

SPONSOR Fatol Arzneimittel GmbH

INDICATION UNDER STUDY Resistant malaria

OBJECTIVES 1) To compare the efficacy of Cotrifazid versus Lariam (mefloquine) or standard treatment in semi-immune subjects with resistant malaria

2) To compare the tolerance of Cotrifazid versus Lariam or standard treatment in semi-immune subjects with resistant malaria

EXPERIMENTAL DESIGN

OF THE TRIAL Open, block-randomised, comparative

PLANNED SAMPLE SIZE 330 (110 Cotrifazid, 110 Lariam, 110  standard

treatment)

NUMBER OF CENTRES 2

SUBJECT SELECTION CRITERIA Subjects with resistant malaria (any species) with a weight > 5kg

SUBJECT EXCLUSION CRITERIA Pregnant women, infants less than 6 months of age, severe malaria

TREATMENT Cotrifazid (rifampicin, co-trimoxazole, isoniazid)

DOSAGE Subjects > 40 kg : 2 x 2 tablets per day for 7 days

Subjects < 40 kg and > 20kg : 2 x 1 tablet per day for 7d

Subjects < 20 kg : 2 x ½ tablet  per day for 7 d

SCHEDULE Every 12 hours

ROUTE OF ADMINISTRATION Oral

COMPARATOR I Lariam (mefloquine)

DOSAGE Subjects > 60 kg : 6 tabs (3, 2, 1)

Subjects > 40 kg and < 60 kg : 5 tabs (2, 2, 1)

Subjects < 40 kg and > 30 kg : 3 ½ tabs (1 ½ , 1, 1)

Subjects < 30 and > 20 kg : 3 tabs (1, 1, 1)

Subjects < 20 kg and > 10 kg : 1 ½ tabs ( ½ , ½, ½ )

Subjects < 10 kg : ¾ tablet ( ¼ , ¼, ¼ )

SCHEDULE Hour 0, 8, 24

ROUTE OF ADMINISTRATION Oral

COMPARATOR II Standard treatment (presently quinine + Fansidar)

DOSAGE Quinine

Subjects > 60 kg : 3 x 600 mg /day for 5 days Subjects < 60 kg : 3 x 10 mg/kg/day for 5 days

+

Fansidar as a single dose

Subjects > 40 kg : 3 tablets

Subjects < 40 kg and > 30 kg : 2 tablets

Subjects < 30 and > 20 kg 1 ½ tablet

Subjects < 20 kg and > 10 kg 1 tablet

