**9 SUBJECT ANALYSIS POPULATIONS**

All subjects who are randomised to receive either Cotrifazid or the comparators constitute the ‘*intention to treat population’*.

Subjects will be excluded from analysis of *safety* if they do not receive at least one daily dose of Cotrifazid or comparators, and one follow-up visit. Remaining subjects constitute the ‘*safety population’.*

Subjects will be excluded from final analysis of *efficacy* if they do not receive the full dose of Cotrifazid, or the full dose of Fansidar + at least 3 daily dose of quinine, and one follow-up visit. Remaining subjects constitute the ‘*efficacy population’*.

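### The efficacy population requires the full 7-day Cotrifazid course, with no stated check on 8 of its 14 doses, while the standard arm's rule can be met in three days and Lariam has none

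*Protocol*

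**What the plan says.** Section 9 defines three populations: intention-to-treat (everyone randomised), safety, and efficacy. Patients are left out of the final efficacy analysis "if they do not receive the full dose of Cotrifazid, or the full dose of Fansidar + at least 3 daily dose of quinine". Attendance at a follow-up assessment is a further condition. The sentence contains no dosing requirement for Lariam.

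Section 5.1.1.3 gives the course lengths. For the test drug it states "Cotrifazid will be given for 7 days", for the first comparator "Lariam will be given for 24 hours", and for the two parts of the standard treatment "Quinine will be given for 5 days" and, separately, "Fansidar will be given as a single dose at day 0". The synopsis and section 5.1.1.1 put Cotrifazid at 12-hour and quinine at 8-hour intervals.

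On observation of dosing, section 5.1.1.4 states: "The administration of the drug for the first three days will be supervised by the nurse in charge of the trial". It adds only that supplies go back to the manufacturer. Section 5.1.2 puts administration times on the case report form without saying who records doses taken away from the nurse. Sections 2.1 and 5.2.1 schedule no routine visit between hour 72 and day 7. Section 2.1 allows a change to the standard treatment for intolerance, clinical worsening or rising parasitaemia. Under section 6.1, a patient with complications changes treatment if on Cotrifazid or Lariam but continues if already on the standard treatment.

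The trial is open (section 4.2), the hypothesis is non-inferiority of the cure rate (section 10.1), and section 10.3 sets 86% as acceptable against an assumed 95%.

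**The concern.** The three arms qualify for the efficacy population on different terms. Cotrifazid needs the whole course, the standard arm needs a shortened minimum, and Lariam needs nothing beyond follow-up. Only the Cotrifazid rule reaches into days with no described supervision.

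Two consequences follow. First, whether a Cotrifazid patient completed days 4-7 has to be settled by a method the protocol does not name, in a trial where staff know the arm and may know the course of the illness. Second, and independently of how well doses are observed, a Cotrifazid patient whose treatment is changed for failure on days 4-7 has by definition not had the whole course and is excluded. A standard-arm patient who fails after day 3 has already qualified and is counted as a failure.

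Removing failures from the test arm alone moves a non-inferiority comparison towards the conclusion the trial hopes to reach.

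**Working it through.** The protocol gives no figure for this point, so there is none to reproduce. The check counts doses and then illustrates the possible size.

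**Doses inside the supervised window** (doses given before hour 72)

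- Cotrifazid: 7 days x 2 = 14 doses, at hours 0, 12, ..., 156. Six fall before hour 72: 6/14 = 43%. The other 8 (57%) fall after it. Above 40 kg ("2 x 2 tablets per day for 7 days") this is 12 of 28 tablets.
- Quinine: 5 days x 3 = 15 doses, at hours 0, 8, ..., 112. Nine fall before hour 72: 9/15 = 60%. Read as three days' dosing, the section 9 minimum is 3 x 3 = 9 doses.
- Fansidar: one dose on day 0.
- Lariam: three doses, at hours 0, 8 and 24, all before hour 72.

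| Arm | Doses needed for section 9 | Of these, after the first three days |
|---|---|---|
| Cotrifazid | 14 of 14 | 8 |
| Standard | 1 Fansidar + 9 of 15 quinine | 0 |
| Lariam | none stated | 0 |

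**How easily the Cotrifazid rule is missed** (assumed per-dose adherence q, doses independent). The share taking all 8 later doses is q^8: 92% at q = 0.99, 85% at 0.98, 66% at 0.95 and 43% at 0.90.

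**Effect of removing failures from one arm.** The implied margin is 95 - 86 = 9 points. Take true Cotrifazid success of 86%, that is 14 failures per 100, and let an assumed share s of those failures be excluded as incomplete courses:

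apparent success = 1 - (14 - 14s)/(100 - 14s)

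- s = 0.25: 1 - 10.5/96.5 = 89.1%, a shift of 3.1 points. The gap to 95% becomes 5.9 points.
- s = 0.50: 1 - 7/93 = 92.5%, a shift of 6.5 points. The gap to 95% becomes 2.5 points.

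**The opposite error.** If unconfirmed doses are assumed taken, non-adherence is counted against the drug. With an assumed 10-30% of courses incomplete and success of 80% instead of 95% in those patients, the cost is 0.10 x 15 = 1.5 to 0.30 x 15 = 4.5 points.

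**Loss of numbers alone.** After 10% loss, 110 x 0.9 = 99 patients per arm remain. At true success of 95% in both arms and one-sided 5%, power = Φ(0.09/√(0.0475/n₁ + 0.0475/99) - 1.645), where 0.0475 = 0.95 x 0.05. It is 90% with n₁ = 99 and 86% if only 80% of Cotrifazid patients qualify (n₁ = 79.2). Selective exclusion matters more than lost power.

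**The case against.** Several stronger readings are tempting, and the protocol does not support them.

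- *Completion cannot be measured.* A reader might infer this from the short supervised period. But administration times go on the case report form (section 5.1.2), the day-7 visit comes after the last scheduled Cotrifazid dose at hour 156, supplies are returned, and withdrawals need a documented reason (section 6.1). An unverified measure is possible. What is missing is any statement of which source decides.
- *The comparators are fully observed.* The supervision sentence speaks of the drug, under a heading about the trial drug, and names no arm. Elsewhere that term means Cotrifazid. Supervision of quinine and Lariam is therefore not established. The supportable statement is only that the standard-arm minimum and the Lariam course can both fall within three days.
- *Staff will decide membership by questioning patients after the outcome is known.* Nothing says so. It is one possibility that the text leaves open.

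It is also fair to say that sicker patients are seen more often (sections 2.1 and 5.2.1), so the contact gap is smaller where it matters most. Home dosing after three supervised days is a reasonable field choice. The 25-50% and 10-30% rates have no anchor in the protocol. The opposite error works against Cotrifazid, so the net direction is not certain. Section 9 does define an intention-to-treat population that needs no adherence data.

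These points limit the claim without removing it. Better observation would not cure the unequal rules, because a patient switched for failure on days 4-7 is excluded even when every dose is witnessed. Section 9 ties the final efficacy analysis to the efficacy population, and section 10.4 assigns the intention-to-treat population to no comparison. An analysis plan could add that assignment, but it could not recover dosing data that were never collected.

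**Conclusion.** The point holds in this form: the completion rules in section 9 differ by arm, and only the Cotrifazid rule depends on doses (8 of 14) that fall after the described supervision and have no stated means of confirmation. In an open non-inferiority trial, this lets Cotrifazid failures on days 4-7 leave the efficacy analysis while comparator failures at the same time remain.

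The dose counts follow directly from the protocol. The effect on the result does not. The shift of 3.1-6.5 points against an implied margin of 9 assumes true success of 86%, removal of 25-50% of Cotrifazid failures and no matching removal in the comparators. It shows that the mechanism could matter and is not a forecast.

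The point gives no ground for calling the sample size inadequate. From the stated inputs, 73 evaluable patients per arm (82 with 10% loss) are enough at one-sided 5% and 80% power, and 110 are planned. The plan should be changed here, but the defect is not fatal, given the intention-to-treat population already defined.

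**What to change.** 1. **Day-7 record.** At the existing day-7 visit, record remaining tablets and any missed doses, with dates, for every patient whose course runs past the supervised days. Do this before the day-7 film is read. For intramuscular quinine, use the injection record. Base adherence status on this and the supervised-dose record, and state in section 5.1.1.4 which arms the supervision sentence covers.
2. **Section 9.** State a comparable completion rule for all three arms, including Lariam. One form is: took the allocated doses due up to the end of the course or to treatment failure, whichever came first. Count a patient whose treatment was changed or stopped for failure as a treatment failure, not as an exclusion. Item 1 without this change would leave the unequal exclusion of failures in place.
3. **Section 10.4.** Report the non-inferiority comparison in the intention-to-treat population alongside the efficacy population, and discuss any disagreement between them.

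The cost is about one line on the case report form at a visit that already takes place, plus edits to the text. A tablet count can overstate adherence, and recording before the film is read does not blind staff in an open trial with earlier films. None of this alters dosing, supervision or patient care.

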**5.1.2 Assignment to Drug or Comparator Groups**

An independent person will generate a randomisation list from a computer program with treatment allocation by block of 12 ; he will assign a unique code number for each person (1-330). The treatment allocation will be written, and kept in an envelope that will be opened once the subject has given his/her consent.

The time of treatment administration will be written on the case report form.

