**2 GENERAL DESIGN**

**2.1 Overall Design**

This is an open, block-randomised, comparative, multicentric study.

All subjects presenting at the outpatient clinic or admitted in the ward of the Maprik Hospital and Yagaum Health Center who are diagnosed with malaria (history of fever and no other major symptom, OptiMAL test positive) and have been already treated for malaria in the last 28 days can be included if they give their informed consent and if the clinician in charge would have given the standard treatment for resistant malaria in the absence of the study. A patient should not be included if the clinician prefers to use quinine for whatever reason, if the patient has one of the symptoms or signs of complicated or severe malaria (i.e. history of recent convulsion, any neurological sign or impairment of consciousness, temperature >40 C0, heavy vomiting, haemoglobinuria, respiratory distress, bleeding, circulatory collapse, shock, jaundice, haemoglobin < 5 g/dl), has contra-indications for mefloquine (history of psychiatric disorder, epilepsy), is less than 6 months of age, or is pregnant. The patients will be randomised on the spot to have either Cotrifazid, Lariam or standard treatment (at present quinine + Fansidar). The treatment dosage and schedule for Cotrifazid will be the following : subjects > 40 kg : 2 x 2 tablets, subjects < 40 kg and > 20kg : 2 x 1 tablet, subjects < 20 kg : 2 x ½ tablet, ever 12 hours for 7 days. The treatment dosage and schedule for Lariam will be the following : subjects > 60 kg : 6 tabs (3 at hour 0, 2 at hour 8, 1 at hour 24), subjects > 40 kg and < 60 kg : 5 tabs (2, 2, 1), subjects < 40 kg and > 30 kg : 3 ½ tabs (1 ½ , 1, 1), subjects < 30 and > 20 kg : 3 tabs (1, 1, 1), subjects < 20 kg and > 10 kg : 1 ½ tabs ( ½ , ½, ½ ), subjects < 10 kg : ¾ tablet ( ¼ , ¼, ¼ ). Follow-up assessments will be done at hours 24, 48 and 72 (clinical, parasitological and pharmacological), and days 7 (clinical, parasitological, biochemical, and pharmacological) and 14 (clinical, parasitological, haematological, and pharmacological), or more intensively in case of persisting symptoms or pathological signs. Treatment will be changed to the standard treatment (at present quinine + Fansidar) if necessary (problems of tolerance, aggravation of clinical status, increase in parasitaemia etc).

All blood samples will be taken by venepuncture (2 ml).

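### One list in a disclosed fixed block of 12, with no rule for dividing it between two open-label centres, leaves either some allocations foreseeable or balance by centre to chance

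*Protocol*

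**What the plan says.** Section 5.1.2 of the protocol describes a single list: "An independent person will generate a randomisation list from a computer program with treatment allocation by block of 12". The same person numbers it in one range: "he will assign a unique code number for each person (1-330". On concealment it says: "The treatment allocation will be written, and kept in an envelope that will be opened once the subject has given his/her consent". It does not call the envelopes sealed or opaque, or say that they are used in number order.

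Section 2.2 names two sites in different provinces: "This is a multiple centre study which will take place at the Maprik Hospital, East Sepik Province, and at Yagaum Health Center". No section stratifies by centre or says how the 330 numbers are shared between the sites.

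Section 4.2 makes the trial open: "Investigators and subjects are aware of the treatment allocation, i.e. Cotrifazid, Lariam or standard treatment". Randomisation takes place at the point of care (Section 2.1): "The patients will be randomised on the spot to have either Cotrifazid, Lariam or standard treatment". Section 2.1 and the synopsis also contain a discretionary bar to entry: "A patient should not be included if the clinician prefers to use quinine for whatever reason". This bar does not appear in the formal exclusion list in Section 3.3.

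Section 3.4 requires a log of the eligibility of everyone screened, whether or not they enter.

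**The concern.** In an open trial each past allocation is known. With a fixed block size that investigators can read in their own protocol, someone who tracks a block can narrow down, and sometimes work out, the next arm. Concealing the envelope does not prevent this, because the inference comes from earlier allocations.

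Prediction does harm only if it can change who enters. The quinine-preference rule offers that route. It is applied before consent, has no stated criteria, and concerns a drug that belongs to one randomised arm. A clinician who expects a particular arm next, and is uneasy about the patient at hand, can keep that patient out without departing from the protocol. Arms would then differ in prognosis at entry. The comparison is one of non-inferiority, with an implied margin of 95% − 86% = 9 percentage points (Section 10.3).

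The second issue is centre. With no centre strata and no rule for dividing the list, the arms may be unevenly spread over two sites in different provinces.

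**Working it through.** **Inputs.** Block of 12 with three equal arms, so 4:4:4 (Section 5.1.2; 110 per arm in Section 10.3). List of 330. Two centres (Section 2.2). The protocol gives no centre shares, so 50:50, 70:30 and 80:20 are assumptions.

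**Reading A: each centre works through whole blocks.**
- An allocation is certain when only one arm remains in the block. The last place is always certain. The last two places hold the same arm with probability 3/11, the last three with 3/11 × 2/10 = 6/110, and the last four with 6/110 × 1/9 = 6/990.
- Expected certain allocations per block: 1 + 3/11 + 6/110 + 6/990 = 1.333. As a share: 1.333/12 = 11.1%, or about 37 of 330.
- Exact recursion over the block: at least one arm is used up for 28.9% of allocations (about 95 of 330). Guessing the arm with most places left is right 51.2% of the time, against 33.3% by chance.
- Balance within a centre is nearly kept. The gap between the largest and smallest arm is at most 4 if each centre's run starts at a block boundary, and slightly more if a block is split.

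**Reading B: both centres draw on one interleaved list, each seeing only its own allocations.** Simulated, with each patient falling to a centre at random:

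| Share of the centre that is guessing | Best guess right | Certain |
|---|---|---|
| 50% | 40% | 0.05% |
| 70% | 43% | 0.6% |
| 80% | 45% | 1.9% |

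| Assumed split | Median gap within a centre | 95th percentile | Gap of 10 or more |
|---|---|---|---|
| 50:50 | 8 | 17 | 41% |
| 70:30 | 8 | 16 | 36% |
| 80:20 | 7 | 14 | 24% to 26% |

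A repeat run at 50:50 with 10,000 lists gave a median of 8, a 95th percentile of 18 and 41%. If the centres share their allocations, prediction returns to the level of Reading A.

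**Does shortening or varying the block help?** Exact recursion for fixed blocks: a block of 6 gives a best guess of 56% with 20% certain, and a block of 3 gives 61% with 33% certain. Shorter fixed blocks are therefore worse. For varied sizes I simulated a clinician who knows no sizes and always guesses the least-used arm, on a list of 165 per centre (330/2, an assumption):
- fixed 12: 51%
- 3, 6 and 9 at random: about 55%
- 9, 12 and 15 at random: 51%

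With 9, 12 and 15 the guess rate stays where it is for fixed 12, but the clinician no longer knows where a block ends. The largest possible gap within a centre is 5, since a block of 15 holds five of each arm.

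**The case against.** The strongest reply is that the two harms rest on opposite readings. If blocks run within a centre, prediction is at its worst but centre balance is nearly assured. If the list is interleaved, balance suffers but prediction is weak. That is correct, and a reader who infers that both apply at full strength goes beyond the protocol, which does not say how the list is divided.

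It is also fair that most allocations stay uncertain. Even under Reading A, about eight in nine are not certain, and for 71% no arm is ruled out. Twelve is a fairly long block for three arms.

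The protocol has safeguards. An independent person makes the list, the envelope is opened only after consent, and the screening log could reveal selective exclusion afterwards. These limit the harm. They do not stop inference from known allocations, and the quinine rule operates before consent.

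Three stronger readings are tempting and do not hold:
- Clinicians may exclude anyone at will. The rule covers a preference for quinine. It is broad, but it is not a general veto.
- The Mantel-Haenszel test in Section 10.4.1.1 requires stratified randomisation. It does not. It can be computed on a single table, and centre can be an analysis stratum whatever the list.
- The list is faulty because 330/12 = 27.5. A half block at the end can leave a gap between arms of at most 4, which is of no practical consequence.

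Finally, no bias in the success rates has been shown. That stands: guess rates measure opportunity, not effect.

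**Conclusion.** The point holds in limited form. As written, Section 5.1.2 has a weakness on either reading. With whole blocks at each centre, about 11% of allocations are certain and a best guess is right 51% of the time. With one interleaved list, the best guess is right 40% to 45% of the time, and the gap between arms within a centre has a median of 7 to 8 and a 95th percentile of 14 to 17.

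The first set of figures assumes that the clinician tracks every allocation in the block and knows where it starts. The second rests on the assumed centre shares and on no exchange of allocations between sites. A reader might infer that the trial's result will be biased, or biased in a given direction. The protocol does not support that: the effect on the comparison against the 9-point margin cannot be calculated from it. Analysis by centre can deal with imbalance between centres, but it cannot remove selection at entry, and no later analysis plan can repair a list already used. This is a cheap improvement worth making before enrolment, not a defect that invalidates the design.

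**What to change.** Before the first patient:

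1. Generate a separate list for each centre, with randomly varied block sizes of about the present length or larger, for example 9, 12 and 15. Do not use 3, 6 and 9, which raise the guess rate to about 55%.
2. Remove the block size from the protocol and hold it with the independent person who makes the list.
3. In Section 5.1.2, require that eligibility (including any decision under the quinine-preference rule) and consent are entered in the Section 3.4 log before the next sequentially numbered, sealed, opaque envelope is opened.
4. Reconcile Sections 2.1 and 3.3, since the quinine-preference rule stands in one and not in the other.
5. In Section 10.4.1.1, name centre as the stratum of the Mantel-Haenszel test.

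The cost is a new list, a new set of envelopes and a short text change. Arm sizes may differ from 110 by a few patients, and the gap between arms within a centre stays at 5 or less. The change does not lower the best-guess rate below the 51% of fixed whole blocks, and that rate is above the 40% to 45% of an interleaved list. What it gains is that block ends are no longer known and that balance by centre is assured.
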